## Methods/Design

### Aims and objectives

This study will compare the effectiveness of a telephone-based health coaching program versus provision of information alone in supporting pregnant women to achieve appropriate gestational weight gain. Pregnant women will be stratified into pre-pregnancy healthy weight and overweight/obese groups. Given the evidence around issues related to excessive weight gain in pregnancy, a pure control group was not included in the study as it was considered inappropriate to not provide information that could be beneficial to maternal and neonatal health.

The hypothesis of the study is that, pregnant women enrolled in the coaching program will be more likely to achieve a healthy gestational weight gain during pregnancy and better maintain their pre-pregnancy weight post pregnancy. Weight-gain that is above the IOM guidelines is considered excessive gestational weight-gain.

The primary objectives of the study are to:i)Compare the differences in gestational weight gain and weight retention at 12 months post birth of participants in the health coaching and information only armsii)Understand the acceptability and experiences of telephone-based coaching amongst pregnant women and antenatal service providers.

As secondary objectives, the study will:iii)Compare changes in diet (fruit, vegetable, fast food and sweetened drink intake)iv)Assess the predictors of service participation and retentionv)Explore service usage patterns such as length of calls and preferred timevi)Assess confidence to changevii)Provide recommendations for program improvement.

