### Study design

This study employs a pragmatic stratified cluster randomised design [31] with stratification by healthy weight and overweight/obese pre pregnancy BMI.

Pregnant women in the study will be allocated to either the information only or health coaching group based on the hospital where they present for antenatal care (Fig. 1). This design was selected to obtain results that can be generalised with high external validity and utility in the real world setting. In this study, the trial environment and processes will be as close as possible to how the program would be rolled out if effective. A range of hospitals in both metropolitan and rural settings, of different sizes and maternity service delivery levels have been chosen to test the scalability of the intervention across the state.

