**Fig. 1 Fig1:**
[figure not shown]
Study flowchart

Randomisation of hospitals, stratified by metropolitan and rural regions, will be undertaken using Microsoft Excel 2010© randomisation generator. Two rural hospitals were combined into one unit for randomisation because they are in the same Local Health District and their aggregated total number of births in 2012 was similar to the total of the other rural hospital in the study. Face-to-face training will be provided, by members of the research team, to the midwives and medical officers at each site to describe the study and the program. The hospitals will develop their own processes to integrate the GHiP referral into the first antenatal appointment for pregnant women. As part of this process, hospitals in both arms will be required to include initial discussion on the importance of healthy gestational weight gain, the setting of a target weight-gain range for the woman’s pregnancy (as per IOM recommendations), screening of the woman for exclusion criteria and recruitment of women following consent.

Health coaches (primarily dieticians and exercise physiologists) delivering GHiP will be provided with a day’s face-to-face training by clinical experts in dietetics and maternity care, in addition to their usual training. A list of online resources to support the pregnant women will also be available to all health coaches. The clinical experts will also be available for further consultation as required.

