### Data analysis

#### Primary objectives

All quantitative data analysis will be based on intention to treat principles. Differences between the two study groups in self-reported weight change from pre-pregnancy weight to weight at 36 weeks gestation and 12 months post birth will be tested using the independent samples *t*-test. The proportions of pregnant women who achieve weight gain within the recommended range and those who return to their pre-pregnancy weight 12 months post birth will be analysed using the *X*^2^ test. The adjusted means of the BMI outcomes at 36 weeks gestation and follow up by BMI category will be compared with the pre pregnancy BMI.

Interview data will be analysed using the thematic analysis approach. The transcribed interviews will be coded by the researchers and if there is a disagreement in the classification of interview responses, the researchers will convene as a group to discuss the discrepancies and revise coding categories if needed. Once agreement is reached, themes and sub-themes will be extracted from the data. Data from the interviews will inform the provision of recommendations for program improvement.

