#### Secondary objectives

Predictors of weight gain within the recommended range at 36 weeks of gestation will be analysed using multilevel linear mixed model. Covariance effects of hospital clusters and study arms will be incorporated into the models as random effects. Then the factors that contribute to BMI outcomes at 36 weeks will be determined with demographic variables, socio-economic status, age, pre pregnancy BMI and parity as the fixed effects.

Changes in dietary scores and confidence to change will be analysed using repeated measures analysis of variance, with the type of intervention and data collection point as between and within subject variables respectively.

Participation and retention in the service and preference for time and length of calls will be analysed using descriptive statistics with reference to the qualitative interview data where appropriate. The recommendations for service improvement will be one of the key themes in analysis of the qualitative data. The referral patterns of the hospitals will also be evaluated to assess recruitment rates with reference to the qualitative interviews with the midwives and doctors to identify the potential barriers and solutions to enhance service participation.

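### The trial is described as stratified by pre-pregnancy BMI, but the stated primary arm comparisons do not stratify by or adjust for BMI, and the one analysis by BMI category names no arm

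*Protocol article*

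**What the plan says.** All references are to the protocol article.

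- **Design label.** Study design describes a cluster randomised design "with stratification by healthy weight and overweight/obese pre pregnancy BMI". Aims and objectives says the same of the participants: "Pregnant women will be stratified into pre-pregnancy healthy weight and overweight/obese groups". Sample size sets 177 women in the healthy range and 532 in the overweight or obese range.
- **Randomisation.** The paragraph under Fig. 1 gives the scheme: "Randomisation of hospitals, stratified by metropolitan and rural regions". BMI plays no part in it.
- **Primary arm comparisons** (Data analysis, Primary objectives). Weight change to 36 weeks and to "12 months post birth will be tested using the independent samples *t*-test". The proportion within the recommended range and "those who return to their pre-pregnancy weight 12 months post birth will be analysed using the *X*^2^ test". No stratification by BMI and no adjustment for it is stated.
- **The analysis by BMI category** (same section). "The adjusted means of the BMI outcomes at 36 weeks gestation and follow up by BMI category will be compared with the pre pregnancy BMI". Study arm is not mentioned.
- **Secondary model** (Data analysis, Secondary objectives). A predictor model has "demographic variables, socio-economic status, age, pre pregnancy BMI and parity as the fixed effects". Arm enters differently: "Covariance effects of hospital clusters and study arms will be incorporated into the models as random effects".

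**The concern.** Stratification is normally declared for one of two purposes: to balance a prognostic factor between arms, or to use that factor in the analysis. Here BMI does neither in the text as it stands. When whole hospitals are allocated, a woman's BMI cannot be a stratum of the randomisation, so it could earn its place only in the analysis, and the tests named for the arm comparison leave it out.

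The article itself treats BMI as prognostic. Background reports that in some studies women who were overweight or obese had 2–6 times the risk of excessive gain, and that recommended gain is set by BMI category. If the arms differ in BMI mix, that difference passes into the unadjusted arm difference.

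The analysis that does look at BMI categories is written as a change from pre-pregnancy BMI. At 36 weeks such a change mainly reflects being pregnant. At 12 months it describes retention. Without a contrast between arms, neither shows whether coaching helped, in either BMI group.

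**Working it through.** **1. The article's own figure.** 177 + 532 = 709, one short of 710. This fits a 25/75 split (0.25 × 710 = 177.5; 0.75 × 710 = 532.5), so it is rounding. The total of 710 cannot be reproduced, because no SD, alpha or intracluster correlation is given. Taking the stated 3 kg, 80% power and 60%/30% attrition, and assuming two-sided 5% and no clustering:

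- n per arm = 2 × (1.96 + 0.84)² × SD² / 3², and total = n/0.4 + n/0.7.
- Solved for SD, 710 as a single comparison implies about 10.2 kg; 177 alone implies about 5.1 kg; 532 alone implies about 8.8 kg.

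With a common SD, two separately powered strata would need equal numbers. The 177/532 split therefore looks more like a recruitment quota than two powered comparisons.

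**2. Number of randomised units.** Study setting lists three rural and two metropolitan hospitals, and two of the rural ones are merged for randomisation. That leaves 2 + 2 = 4 units, so two per arm if each region is split evenly. So few units cannot be relied on to even out BMI mix. Each site also builds its own referral process (Study design), and Discussion concedes that local factors may influence recruitment. If attrition is related to BMI, losses of 60% and 30% could separate the analysed groups further.

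**3. Where BMI enters each stated analysis.**

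| Analysis | Compares arms? | Uses BMI? |
|---|---|---|
| t-test on weight change | Yes | No |
| Chi-square, gain within range | Yes | Only in the outcome definition |
| Chi-square, return to pre-pregnancy weight | Yes | No |
| BMI outcomes by BMI category | Not stated | Yes |
| Secondary predictor model | Arm is a random effect | Yes, fixed effect |

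No row gives a fixed arm contrast that is adjusted for BMI or stratified by it.

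**4. Illustration of size.** Shift in the unadjusted arm difference = (gap between arms in overweight/obese share) × (difference in mean gain between BMI groups). Neither input is in the article; both are assumptions.

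- Low: 0.10 × 2 kg = 0.2 kg; 0.2/3 = 7% of the target difference.
- High: 0.20 × 4 kg = 0.8 kg; 0.8/3 = 27%.

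The direction is unknown.

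**5. What a contrast within each BMI group could show.** Assume equal enrolment per arm, no clustering and the stated attrition. SE = SD × √(1/n₁ + 1/n₂); power = Φ(3/SE − 1.96).

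- Healthy weight: 177/2 × 0.4 = 35.4 and 177/2 × 0.7 = 61.95 completers. Power is 81%, 66% and 53% at assumed SDs of 5, 6 and 7 kg.
- Overweight/obese: 532/2 × 0.4 = 106.4 and 532/2 × 0.7 = 186.2 completers. Power is 99.9%, 98% and 94%.

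Clustering would lower all of these. The interaction contrast has a larger standard error than either stratum alone, which is why it should be labelled exploratory.

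**The case against.** **BMI is already in a primary outcome.** A reader might infer that the primary analysis ignores BMI altogether. It does not: the recommended range is BMI-specific, and gain within that range is the outcome closest to the hypothesis. This stands as a limit on the point. It does not adjust the comparison, and it does nothing for the t-test in kilograms. Excessive gain is defined in the article against the same BMI-specific guidelines, yet Background still reports a risk that differs by BMI, so the definition does not remove the dependence.

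**No stated aim is left unmet.** A reader might infer that a comparison of coaching within each BMI group was promised and then dropped. No numbered objective says so; the first is an overall arm comparison. The fair statement is that a declared stratifier goes unused in that comparison.

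**The before-after sentence is loosely worded.** Its adjusted means are unexplained and may have been intended to include arm. If so, this needs to be written. Nor can one say that the comparison would be significant in both arms regardless of coaching: that is a reasonable expectation at 36 weeks, but nothing in the article supports it at 12 months.

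**Imbalance may be small.** Randomisation is within region, and Study setting says the women's demographic characteristics are similar within the metropolitan and rural groups. BMI is not named, but this may reduce the gap. Site-level BMI quotas could also be in the full protocol, so it would go too far to say that nothing balances BMI.

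**An unadjusted test is not an error in itself, and covariates are often left to the analysis plan.** Both are true in general. Here, however, the article names the primary tests and declares the stratifier, and the two do not meet. The point rests on what is written, not on silence.

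**Conclusion.** The point holds as a mismatch between declared design and stated analysis. BMI is announced as the stratifier and used for recruitment numbers, region is what stratifies the randomisation, and no stated arm comparison uses BMI beyond the definition of the recommended range. The one analysis by BMI category, as written, does not compare arms. The secondary predictor model does not repair this, because arm is a random effect there.

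The consequence is a plausible but unquantified imbalance. The 0.2–0.8 kg range rests entirely on assumed inputs. Imbalance arising from the allocation is chance imbalance under random assignment, so the range should not be read as a demonstrated or systematic bias. The finding about wording and choice of analysis is firm; the size is not. It should be corrected, but it does not by itself invalidate the trial.

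**What to change.** 1. Include pre-pregnancy BMI, as category or continuous, as a woman-level covariate in the primary arm comparison, with arm as a fixed effect, in a model that also allows for hospital clustering. The primary section has no such model at present; with four units, how to handle clustering is a separate and larger question that must be settled alongside. Use the corresponding adjusted analysis for the two proportions.
2. Replace the comparison with pre-pregnancy BMI by the arm difference in weight or BMI change within each BMI category, at 36 weeks and at 12 months, with an arm-by-BMI interaction reported as exploratory.
3. Reword Aims and objectives and Study design to say that region is the randomisation stratum and BMI is a recruitment and analysis stratum.

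Adding age, parity and socio-economic status is optional.

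The cost is a change of analysis wording. Pre-pregnancy BMI is already needed for eligibility and already listed in the secondary model, so no new data are required and the sample size is unaffected.

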#### Secondary objectives

Predictors of weight gain within the recommended range at 36 weeks of gestation will be analysed using multilevel linear mixed model. Covariance effects of hospital clusters and study arms will be incorporated into the models as random effects. Then the factors that contribute to BMI outcomes at 36 weeks will be determined with demographic variables, socio-economic status, age, pre pregnancy BMI and parity as the fixed effects.

Changes in dietary scores and confidence to change will be analysed using repeated measures analysis of variance, with the type of intervention and data collection point as between and within subject variables respectively.

Participation and retention in the service and preference for time and length of calls will be analysed using descriptive statistics with reference to the qualitative interview data where appropriate. The recommendations for service improvement will be one of the key themes in analysis of the qualitative data. The referral patterns of the hospitals will also be evaluated to assess recruitment rates with reference to the qualitative interviews with the midwives and doctors to identify the potential barriers and solutions to enhance service participation.

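### The secondary predictor model enters study arm as a random effect and gives one linear model to a yes/no and a continuous outcome, while the objective on predictors of participation and retention has no predictor analysis

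*Protocol article*

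**What the plan says.** All references are to the protocol article.

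- **Outcome and model** (Data analysis, Secondary objectives): "Predictors of weight gain within the recommended range at 36 weeks of gestation will be analysed using multilevel linear mixed model".
- **Second outcome, two sentences later:** "Then the factors that contribute to BMI outcomes at 36 weeks will be determined".
- **Random effects:** "Covariance effects of hospital clusters and study arms will be incorporated into the models as random effects".
- **Fixed effects:** "demographic variables, socio-economic status, age, pre pregnancy BMI and parity as the fixed effects". Arm is not in this list.
- **The in-range endpoint in the primary analysis** (Data analysis, Primary objectives): "The proportions of pregnant women who achieve weight gain within the recommended range" are compared with a chi-square test, so the endpoint is treated there as yes/no.
- **Objective iv** (Aims and objectives): the study will assess "the predictors of service participation and" retention.
- **Analysis given for objective iv** (Secondary objectives): "Participation and retention in the service and preference for time and length of calls will be analysed using descriptive statistics", with reference to the interviews where appropriate. Hospital referral patterns are also to be evaluated, to find barriers to participation.

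**The concern.** Three statements in one section do not fit the design, the endpoint or the objective.

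1. **Arm as a random effect.** A random effect treats its levels as draws from a population whose variance is of interest. The two service models are not such draws; they are the contrast that the trial randomises. The next paragraph of the same section treats the allocated intervention as an ordinary between-subjects factor in the repeated-measures analysis, so the plan handles arm in two incompatible ways.
2. **One linear model for two kinds of outcome.** Gain within range is yes/no and BMI is continuous. An analyst cannot tell which outcome the model serves. If it is the first, a linear model implies constant residual variance and can give fitted probabilities outside 0 to 1.
3. **Objective without a matching analysis.** An objective on predictors needs an analysis that relates characteristics to the outcome. None is stated for participation or retention. Retention matters in this trial because the Sample size section expects 60% attrition with coaching and 30% with information only.

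At stake are how well the secondary model is defined and whether objective iv gets an answer. The primary comparison is not affected by this point.

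**Working it through.** The plan gives no figure for this model, so there is none to reproduce. The check is mainly one of reading; the arithmetic shows how much each fault matters.

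**Step 1. Information on an arm variance.** There are two arms (Abstract), so the variance has 2 - 1 = 1 degree of freedom (df). The 95% limits for a variance, as multiples of its estimate, are df/χ²(0.975, df) and df/χ²(0.025, df).
- Lower: 1/5.024 = 0.199
- Upper: 1/0.000982 = about 1018

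This is the favourable case, because it ignores the error in the arm means.

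**Step 2. The hospital term that should stay.** Five hospitals form four randomised units, because two rural hospitals were combined (Study design). Assume two units per arm, as the metropolitan/rural stratification implies. Within-arm unit variance then has 4 - 2 = 2 df.
- Lower: 2/7.378 = 0.27
- Upper: 2/0.0506 = about 39.5

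This variance can be estimated, but only weakly, so a small-sample correction is needed.

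**Step 3. Effect on the predictors.** In 150 simulated trials the outcome was continuous, with one individual-level predictor and a true coefficient of 1. Assumed: SD 6 kg, intraclass correlation (ICC) 0.02, a 3 kg arm effect, and 142 and 248 completers.

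| Arm entered as | Mean coefficient | Mean standard error |
|---|---|---|
| random | 1.028 | 0.301 |
| fixed | 1.029 | 0.300 |

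The predictor result barely moves. Covariates that differ strongly between arms or hospitals could be affected more.

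**Step 4. Illustration only: if someone read an arm contrast from this model.** The article gives neither SD nor ICC; SD 6 kg and ICC 0 to 0.05 are assumptions. With 710 women split equally, completers are 355 × 0.4 = 142 and 355 × 0.7 = 248.5, with hospitals split 2 and 3. For an observed difference d with sampling variance v, the predicted contrast is d × (1 - v/d²), or zero if d² < v.
- At ICC 0.02 the between-hospital variance is 0.02 × 36 = 0.72 and the within-hospital variance is 35.28.
- v = 35.28/142 + 35.28/248.5 + 0.72/2 + 0.72/3 = 0.99.
- For d = 3: 3 × (1 - 0.99/9) = 2.67 kg.

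Averaged over 200,000 simulated values of d around a true 3 kg:

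| ICC | Mean contrast, arm random (kg) | Arm variance estimated as zero |
|---|---|---|
| 0 | 2.86 | 0.0% |
| 0.01 | 2.75 | 0.5% |
| 0.02 | 2.63 | 2.2% |
| 0.05 | 2.35 | 11.6% |

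With arm fixed the mean is 3.00 kg throughout. These figures concern weight in kg, which is neither of the two outcomes named for this model.

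**Step 5. Objective against analysis.** Objective iv names predictors of two outcomes, participation and retention. The analysis section summarises both and adds interviews and referral patterns. The only predictor model is for weight gain and BMI.

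**The case against.** The strongest defence is that this model is not there to estimate the arm effect. That comparison is assigned to the t-test and chi-square test under Primary objectives; here the listed fixed effects are the predictors of interest. **This stands.** A reader might infer that the trial's treatment effect will be shrunk towards zero. The documents do not support that: no arm contrast is to be reported from this model, and Step 3 shows that its intended output is little changed. That the primary tests name no clustering term is a separate matter and adds no weight here.

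Second, a linear model suits BMI at 36 weeks, so it is not wrong for everything the section names. **This also stands.** The variance fault for the yes/no outcome may be moderate too: if probabilities lie between 0.2 and 0.6 (an assumption), p(1 - p) lies between 0.16 and 0.25. What remains is that one model is given two kinds of outcome, and the section must say which model serves which.

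Third, a reader might say that the predictor model addresses an outcome foreign to the objectives. That does not hold. Gestational weight gain is primary objective i, and achieving a healthy gain is the hypothesis. A predictor analysis of it is a supplement, not an error.

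Fourth, objective iv gets more than tables: interviews, including with women who withdraw, and referral patterns may explain uptake and drop-out. **Partly stands.** These sources can suggest reasons, but no analysis is stated that relates women's characteristics to retention.

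The absence of a separate analysis plan does not excuse these points, since the article states them explicitly and they conflict with other statements in it.

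**Conclusion.** The point holds as a mis-specification of secondary analyses that should be corrected. Arm is explicitly random and absent from the fixed effects, which yields a variance that two levels cannot usefully estimate (limits 0.20 to 1018 times the estimate). This rests on the article's wording and the number of arms alone. The two-outcome conflict and the gap at objective iv follow from comparing sections and need no assumptions.

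The practical size is limited. Individual-level coefficients for a continuous outcome are almost unchanged under the conditions of Step 3. The shrinkage of a 3 kg contrast to between 2.86 and 2.35 kg depends on the assumed SD and ICC, and would matter only if an arm contrast were taken from this model, which the plan does not propose.

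**What to change.** 1. **Arm and clustering.** Enter arm as a fixed effect and keep only hospital or randomisation unit as random. State that four units estimate this variance weakly, and name a small-sample correction.
2. **Outcomes.** Name each outcome with its own model: a logistic mixed model for gain within the recommended range and a linear mixed model for BMI at 36 weeks.
3. **Objective iv, retention.** Add a logistic model for retention or completion among enrolled women, using the baseline factors already listed (demographic variables, socio-economic status, age, pre-pregnancy BMI, parity).
4. **Objective iv, participation.** Keep enrolment descriptive, alongside the interview and referral data, and reword the objective to match, unless covariates are held for women who decline. Recruitment strategies describes eligibility screening of every woman, but nothing shows that socio-economic status or parity is recorded for decliners.

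The cost is analysis wording and one extra model on data already held for enrolled women. Modelling enrolment would not be free if decliners' covariates had to be collected.

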### Sample size

A total of 710 women will be recruited; 177 and 532 pregnant women with a pre-pregnancy BMI of 18.5–24.9 kg/m^2^ (healthy range) and ≥25.0 kg/m^2^ (overweight or obese range) respectively. 248 women will be recruited across the three rural hospitals with 462 recruited at metropolitan hospitals. The higher numbers in metropolitan hospitals is to reflect the larger target population in these areas.

The sample size has been calculated using previous reports of weight gain during pregnancy [10, 13, 33] to detect a difference of 3 kgs in gestational weight gain between intervention and control groups at 80 % power. Attrition rates of 60 % in the coaching arm and 30 % in the information only arm are expected. These rates account for the up to 15 % of women, across both arms, who start the study and go on to develop conditions during pregnancy that exclude them from further participation [34] and, allows for the perception of participant burden in the coaching arm. The relatively high attrition rate is conservative compared with other population based programs.

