### Data collection

#### Quantitative

Data for the study will be collected at baseline (prior to 18 weeks gestation), 36 weeks gestation and 12 months post-birth. Baseline, endpoint and follow up data will be self-reported by the women. These data will include validated dietary [35–37] and physical activity [38, 39] measures. Baseline and endpoint data for the coaching arm will be collected by the health coach for the coaching arm and by a research assistant for the information only arm. Coaching participants who discontinue the coaching program without withdrawing from the study will be contacted by the research assistant for their endpoint data collection. The 12 months post birth data will be collected by the research assistant.

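### The repeated-measures ANOVA for diet and confidence treats the baseline score as an outcome level, which gives up some precision that baseline adjustment would recover

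*Protocol article*

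**What the plan says.** Under Aims and objectives, the first secondary objective of the protocol article is to "Compare changes in diet (fruit, vegetable, fast food and sweetened drink intake"). Assessing confidence to change is a further secondary objective.

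Under Data collection (Quantitative): "Data for the study will be collected at baseline (prior to 18 weeks gestation), 36 weeks gestation and 12 months post-birth". The same paragraph adds "These data will include validated dietary" and physical activity measures. Diet is therefore explicitly measured at baseline. Confidence is not listed there; its baseline value is only implied where the analysis section speaks of change.

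Under Data analysis (Secondary objectives): "Changes in dietary scores and confidence to change will be analysed using repeated measures analysis of variance, with the type of intervention and data collection". The sentence ends by making arm the between-subject factor and visit the within-subject factor. No baseline covariate is named for these outcomes. The text does not say whether the arm main effect or the arm-by-time interaction carries the comparison.

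**The concern.** With data collection point as the within-subject factor, its levels are baseline, 36 weeks and 12 months post-birth. The baseline score, taken before the intervention can act, then sits on the outcome side of the model. The interaction compares changes from baseline, so it carries the full sampling noise of the baseline score. Regressing each follow-up score on baseline removes more of that noise whenever the correlation is below 1.

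Diet is a behaviour that the coaching is meant to change, and heavy attrition is expected. A real difference in diet could be missed for want of precision that the collected data can supply. The model and both of its factors are fixed in the text, so this is a stated choice and not a detail left to another document.

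**Working it through.** **The plan's own figure.** None is given for diet or confidence. The Sample size section says "A total of 710 women will be recruited", planned "to detect a difference of 3 kgs in gestational weight gain between intervention and control groups at 80 % power". That figure concerns weight gain. It cannot be reproduced, because no standard deviation or significance level is stated, and it is not affected by this point.

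**Inputs from the document.** 710 women; attrition of 60% (coaching) and 30% (information only); three collection points.

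**Assumptions.** 355 women per arm (no split by arm is stated); equal variances; the same correlation rho between any two visits, taken as 0.5 with range 0.3 to 0.7 (none is stated); two-sided 5% level; women treated as independent. Variances are in SD² units.

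**Step 1, completers.** 355 × 0.4 = 142 and 355 × 0.7 = 248.5. Effective size n = 1/(1/142 + 1/248.5) = 90.4.

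**Step 2, variance of a single-visit contrast.**
- Change from baseline: 2(1 − rho)/n.
- Baseline-adjusted: (1 − rho²)/n.
- Ratio, adjusted to change: (1 + rho)/2. This is 0.65, 0.75 and 0.85 at rho 0.3, 0.5 and 0.7, a reduction of 35%, 25% and 15%.

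**Step 3, power of the joint tests, like for like.** The effect d at 36 weeks is set so that a 36-week change-score test has 80% power: d = (1.960 + 0.842) × √(2(1 − rho)/n), which is 0.295 SD at rho 0.5. The effect at baseline, 36 weeks and 12 months is d times (0,1,1) if kept, (0,1,0) if lost and (0,1,0.5) if half is kept.
- Planned interaction (2 df): noncentrality n·Σ(e − ē)²/(1 − rho). This is 10.47 if kept or lost and 7.85 if half is kept, at any rho.
- Baseline-adjusted joint test of both visits (2 df): noncentrality n·e′V⁻¹e, where e holds the two follow-up effects and V has 1 − rho² on the diagonal and rho − rho² off it. At rho 0.5 this is 15.70 (kept), 11.77 (lost) and 10.79 (half).

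| rho | Effect at 12 months | Planned interaction | Baseline-adjusted | Gain (points) |
|---|---|---|---|---|
| 0.3 | kept | 83% | 98% | 15 |
| 0.3 | lost | 83% | 90% | 7 |
| 0.3 | half kept | 71% | 91% | 20 |
| 0.5 | kept | 83% | 95% | 12 |
| 0.5 | lost | 83% | 87% | 4 |
| 0.5 | half kept | 71% | 84% | 14 |
| 0.7 | kept | 83% | 91% | 8 |
| 0.7 | lost | 83% | 85% | 2 |
| 0.7 | half kept | 71% | 78% | 8 |

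**Step 4, the arm main effect, if it were read.** It averages the arm difference over three levels, one of which cannot carry an effect. An effect kept at 12 months is estimated as (0 + 1 + 1)/3 = two thirds of its size, and one present only at 36 weeks as one third. With variance (1 + 2rho)/(3n), power at rho 0.5 is 63% and 21%. In 3,000 simulated trials at rho 0.5, a constant 0.30 SD effect gave a main-effect estimate of 0.20 SD.

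**The case against.** **Which term is the test.** A reader might infer that the plan's arm comparison is diluted by the pre-intervention value. The text does not support that. Both the objective and the analysis sentence speak of changes, and in this model differential change is the arm-by-time interaction, which is not diluted. The main-effect figures in step 4 apply only if the wrong term is read. Naming the term is also detail that an article can leave to a fuller document.

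**A larger gain.** A reader might set the baseline-adjusted test at 36 weeks alone (90% power at rho 0.5) against the interaction (83% or 71%) and claim 7 to 19 points. That mixes baseline adjustment with a move from two degrees of freedom to one. The plan names no leading visit for diet, and two coaching calls follow the birth. The fair comparison is the one in step 3.

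**Clustering.** Hospitals are randomised, and two of the five are merged, leaving four units. With four equal units of about 98 completers, m = 98, the share of an arm mean's variance lying between hospitals is ICC/(ICC + (1 − ICC)/m): about 50%, 67% and 84% for an assumed ICC of 0.01, 0.02 and 0.05. The formulas in step 2 describe only the woman-level part. This objection stands: the power figures are upper-end illustrations. The ANOVA names no hospital term either, a separate and larger matter that baseline adjustment does not cure.

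**Stable hospital differences.** With so few units, arms may differ at baseline for lasting reasons. A change contrast removes such differences, whereas a woman-level slope on self-reported scores may not do so fully. This also stands, and it argues for keeping the change contrast as a sensitivity analysis.

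**An efficiency preference.** The interaction is a conventional test of change, and no primary result or sample size depends on it. That lowers the priority. It does not make the planned ANOVA the better choice.

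**Conclusion.** The point holds as a matter of precision. As written, baseline is an outcome level and not a covariate, explicitly so for diet and by implication for confidence. The likely intended test is not biased or diluted by this, but it uses the baseline score less efficiently than adjustment would. At woman level the single-visit variance is 15% to 35% higher than it need be, expressed as a share of the change-score variance. The joint test gives up about 4 to 14 power points at rho 0.5, 7 to 20 at 0.3 and 2 to 8 at 0.7.

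The size depends on the assumed correlation, the equal split by arm and the absence of clustering. With four randomised units the real gain is uncertain and probably smaller. Priority is low.

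**What to change.** In Data analysis (Secondary objectives), replace the repeated-measures ANOVA for each dietary score and for confidence to change with a model of the 36-week and 12-month scores. Its fixed effects are arm, visit, arm-by-visit, the woman's baseline score and baseline-by-visit, with hospital accounted for. Report the arm difference at each visit. State that the arm main effect of any model with baseline among its outcome levels will not be used. State under Data collection that confidence is measured at baseline, if it is. Keep the change-from-baseline contrast as a sensitivity analysis.

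The cost is wording only where the baseline score is already collected, with no further women, visits or staff. Two small downsides remain. A handling rule is needed for women without a baseline score. Adjustment for a self-reported woman-level score may also leave stable differences between hospitals partly in place. The gain further assumes that baseline is recorded before coaching can have an effect.
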